## Data Availability

Not Applicable.

## Appendix 1

**Schedule of Assessments** All times are measured from date of enrollment. Clinical follow-up visits can be ± 6 weeks of the stated time points, scans should be ± 3 weeks

**Table Taba:**

	**Before** **Treatment**	**Year 1**	**Year 2**	**Year 3–5**
History and Physical examination	X*	3, 6, 9, 12 mo	18 mo, 24 mo	36, 48, 60 mo
CT chest	X	3, 6, 12 mo	18, 24 mo	36, 48, 60 mo
Pulmonary Function Testing	X	6,12 mo	24 mo	36, 48, 60 mo
Adverse Event Assessment	X	3, 6, 9, 12 mo	18, 24 mo	36, 48, 60 mo
FACT-L and EQ-5D-5L QOL scoring	X	3, 6, 9, 12 mo	18, 24 mo	36, 48, 60 mo

*Abbreviations*: *mo *months

*including weight and extent of weight loss

## Appendix 2

Example calculations for recovery factor

**Table Tabb:**

Assigned Level	Time since Previous Treatment	Recovery Factor Calculation
Level 1	6 months	10 + 0 = 10%
Level 1	1 year	10 + [0.75% * (6 months)] = 14.5%﻿
Level 1	1 year and 3 weeks	Partial months not included; round down Recovery same as above, 14.5%
Level 1	10 years	No further repair after 5 years; apply 5 years for calculation 10 + [0.75% * ({5 years * 12 months/year} – 6 months)] = 50.5%^†^
Level 3	Two prior courses: Course 1 = 3 years ago Course 2 = 2 years ago	For course 1: 15 + [1% * ({3 years * 12 months/year} – 6 months)] = 45% For course 2: 15 + [1% * ({2 years * 12 months/year} – 6 months)] = 33%

^†^in practice, recovery values will be rounded to the nearest whole number so 14.5￫15% and 50.5￫51%

Example calculation for proximal bronchial tree dose at Level 1

**Table Tabc:**

**Cou****rse**	**Physical Dose**	**EQD2****G****y**	**Recovery**	**Calculation**	**EQD2****G****y** **Applied to Cumulative Plan**
1 (previous course 1 year ago)	60Gy/30	60	15% (see calculation above)	60*0.85	51
2 (current course)	30Gy/10	36	0%	N/A	36
Total					87 < 88 EQD2Gy

*note point dose calculations are not sufficient for this trial; full 3D EQD2 dose evaluation based on dose distribution is required; the table above is for illustrative purposes of the dose scaling and dose constraint only

## Appendix 3

Calculated recovery factors per month

**Table Tabd:**

Months	Level −1	Level 0	Level 1	Level 2	Level 3	Level 4	Level 5	Level 6
1	N/A	N/A	N/A	N/A	N/A	N/A	N/A	N/A
2	N/A	N/A	N/A	N/A	N/A	N/A	N/A	N/A
3	N/A	N/A	N/A	N/A	N/A	N/A	N/A	N/A
4	N/A	N/A	N/A	N/A	N/A	N/A	N/A	N/A
5	N/A	N/A	N/A	N/A	N/A	N/A	N/A	N/A
6	3%	10%	10%	15%	15%	20%	20%	25%
7	4%	11%	11%	16%	16%	21%	21%	26%
8	4%	11%	12%	17%	17%	22%	23%	28%
9	5%	12%	12%	17%	18%	23%	24%	29%
10	5%	12%	13%	18%	19%	24%	25%	31%
11	6%	13%	14%	19%	20%	25%	26%	32%
**12**	**6%**	**13%**	**15%**	**20%**	**21%**	**26%**	**28%**	**33%**
13	7%	14%	15%	20%	22%	27%	29%	35%
14	7%	14%	16%	21%	23%	28%	30%	36%
15	8%	15%	17%	22%	24%	29%	31%	38%
16	8%	15%	18%	23%	25%	30%	33%	39%
17	9%	16%	18%	23%	26%	31%	34%	40%
18	9%	16%	19%	24%	27%	32%	35%	42%
19	10%	17%	20%	25%	28%	33%	36%	43%
20	10%	17%	21%	26%	29%	34%	38%	45%
21	11%	18%	21%	26%	30%	35%	39%	46%
22	11%	18%	22%	27%	31%	36%	40%	47%
23	12%	19%	23%	28%	32%	37%	41%	49%
**24**	**12%**	**19%**	**24%**	**29%**	**33%**	**38%**	**43%**	**50%**
25	13%	20%	24%	29%	34%	39%	44%	52%
26	13%	20%	25%	30%	35%	40%	45%	53%
27	14%	21%	26%	31%	36%	41%	46%	54%
28	14%	21%	27%	32%	37%	42%	48%	56%
29	15%	22%	27%	32%	38%	43%	49%	57%
30	15%	22%	28%	33%	39%	44%	50%	59%
31	16%	23%	29%	34%	40%	45%	51%	60%
32	16%	23%	30%	35%	41%	46%	53%	61%
33	17%	24%	30%	35%	42%	47%	54%	63%
34	17%	24%	31%	36%	43%	48%	55%	64%
35	18%	25%	32%	37%	44%	49%	56%	66%
**36**	**18%**	**25%**	**33%**	**38%**	**45%**	**50%**	**58%**	**67%**
37	19%	26%	33%	38%	46%	51%	59%	68%
38	19%	26%	34%	39%	47%	52%	60%	70%
39	20%	27%	35%	40%	48%	53%	61%	71%
40	20%	27%	36%	41%	49%	54%	63%	73%
41	21%	28%	36%	41%	50%	55%	64%	74%
42	21%	28%	37%	42%	51%	56%	65%	75%
43	22%	29%	38%	43%	52%	57%	66%	77%
44	22%	29%	39%	44%	53%	58%	68%	78%
45	23%	30%	39%	44%	54%	59%	69%	80%
46	23%	30%	40%	45%	55%	60%	70%	81%
47	24%	31%	41%	46%	56%	61%	71%	82%
**48**	**24%**	**31%**	**42%**	**47%**	**57%**	**62%**	**73%**	**84%**
49	25%	32%	42%	47%	58%	63%	74%	85%
50	25%	32%	43%	48%	59%	64%	75%	87%
51	26%	33%	44%	49%	60%	65%	76%	88%
52	26%	33%	45%	50%	61%	66%	78%	89%
53	27%	34%	45%	50%	62%	67%	79%	91%
54	27%	34%	46%	51%	63%	68%	80%	92%
55	28%	35%	47%	52%	64%	69%	81%	94%
56	28%	35%	48%	53%	65%	70%	83%	95%
57	29%	36%	48%	53%	66%	71%	84%	96%
58	29%	36%	49%	54%	67%	72%	85%	98%
59	30%	37%	50%	55%	68%	73%	86%	99%
**60**	**30%**	**37%**	**51%**	**56%**	**69%**	**74%**	**88%**	**100%**

## Appendix 4

### Adverse event definition and reporting

An adverse event (AE) or reaction is any unfavorable and unintended sign (including an abnormal laboratory finding), symptom, or disease temporally associated with the use of a medical treatment or procedure that may or may not be considered related to the medical treatment or procedure.

A serious adverse event (SAE)or reactionas defined in the ICH Guideline: Clinical Safety Data Management: Definitions and Standards for Expedited Reporting, E2A Section IIB includes any untoward medical occurrence that at any dose:

- Results in death
- Is life-threatening (refers to an event in which the patient was at risk of death at the time of the event; it does not refer to an event which hypothetically might have caused death if it were more severe.)
- Results in persistent or significant disability/incapacity
- Requires in-patient hospitalization or prolongation of existing hospitalization
- Is a congenital anomaly/birth defect

Important medical events that may not be immediately life-threatening or result in death or hospitalization may be considered a serious adverse event, when, based upon medical and scientific judgment, they may jeopardize the patient or may require intervention to prevent one of the other outcomes listed in the definition above. Unexpected adverse reaction is one that the nature and severity is not consistent with the applicable product information (e.g., Investigator’s Brochure or Product Monograph, described in the REB/IRB approved research protocol or informed consent document), or occurs with more than expected frequency.

All AEs will be collected starting at baseline. There is no time-limit for collection of AEs and SAEs after treatment within the 5-year follow-up period (e.g. a treatment-related complication at four years post-treatment will still be captured). All AEs are to be captured during treatment and only study-related AEs in the follow-up period.

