### Adverse events

Full details of adverse event collection and reporting are provided in Appendix 4. The severity of adverse events will be evaluated using the Common Terminology Criteria for Adverse Events (CTCAE) version 5.0 (http://ctep.cancer.gov).

In the absence of recurrence, any grade 3–5 toxicity listed in Table 3 will automatically be considered to be possibly, probably or definitely related to treatment (i.e. meeting the primary endpoint), unless there is clear evidence that the adverse event is either unrelated or unlikely to be related. The latter instance may occur, for example, in the case of a cardiac event in a patient with an upper lobe tumor and negligible heart dose, or esophageal issues in a patient who received negligible esophageal dose. If a patient starts a drug therapy with overlapping side effects, toxicity may be attributed to the new drug. If there is uncertainty, a final decision will be made by the members of the Data Safety Monitoring Committee (DSMC). See below for causality definitions.

**Table 3 Tab3:** Examples of treatment related adverse events

Structure	Adverse Event
Cardiac and Pericardial	Constrictive pericarditis
	Symptomatic pericardial effusion
	Pericardial tamponade
	Pericarditis
Gastrointestinal	Esophageal fistula
	Esophageal ulceration
	Esophageal dysmotility
	Esophageal hemorrhage
	Esophageal necrosis
	Esophageal obstruction
	Esophageal stenosis
	Esophageal perforation
Pulmonary/mediastinal	Atelectasis—symptomatic
	Bronchial fistula
	Bronchial obstruction
	Bronchopleural fistula
	Bronchopulmonary hemorrhage
	Dyspnea
	Pneumonitis
	Tracheal/Pulmonary fistula
	Tracheal stenosis
	Mediastinal hemorrhage

In the setting of a recurrence, if a patient develops symptoms of an adverse event but deemed on balance more likely caused by a tumor recurrence than treatment (e.g. pulmonary hemorrhage in the presence of recurrence), this will NOT be considered a treatment-related toxicity.

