### Follow-up evaluation

Patients will be seen in follow-up as outlined in Appendix 1 (every 3 months in year 1, every 6 months in year 2 then annually to 5 years). At each visit, a history and physical examination will be conducted by the oncologist, and CTCAE version 5.0 study treatment related toxicities recorded. Also, the quality-of-life questionnaire will be completed.

CT chest will be repeated at 3, 6, 12, 18 and 24 months then annually to 5 years. Additional imaging or laboratory investigations may be carried out at the discretion of the oncologist. Pulmonary function tests will be repeated at 6, 12 and 24 months then annually. Following progression of disease, future CT scans are optional.

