#### Causality (attribution)

In the absence of recurrence, any Grade 3-5 toxicity listed below will automatically be considered to be possibly, probably or definitely related to treatment (i.e. meeting the primary endpoint), unless there is clear evidence that the adverse event is either unrelated or unlikely to be related. The latter instance may occur, for example, in the case of a cardiac event in a patient with an upper lobe tumor and negligible heart dose, or esophageal issues in a patient who received negligible esophageal dose. If a patient starts a drug therapy with overlapping side effects, toxicity may be attributed to the new drug. If there is uncertainty, a final decision will be made by the members of the Date Safety Monitoring Committee (DSMC). See below for causality definitions.

In the setting of a recurrence, if a patient develops symptoms of an adverse event but deemed on balance more likely caused by a tumor recurrence than treatment (e.g. pulmonary hemorrhage in the presence of recurrence), this will NOT be considered a treatment-related toxicity.

An adverse event or reaction is considered related to the research intervention (i.e. radiotherapy) if there is a reasonable possibility that the reaction or event may have been caused by the research intervention (i.e. a causal relationship between the reaction and the research intervention cannot be ruled out by the investigator(s)). The relationship of an AE to the study treatment (causality) will be described using the following definitions:

- Unrelated: Any adverse event for which there is evidence that an alternative etiology exists or for which no timely relationship exists to the administration of the study treatment and the adverse event does not follow any previously documented pattern. The adverse event, after careful consideration by the investigator, is clearly and incontrovertibly due to causes other than the intervention.
- Unlikely: Any adverse event for which the time relationship between the study treatment and the event suggests that a causal relationship is unlikely and/or the event is more likely due to the subject’s clinical condition, or other therapies concomitantly administered to the subject.

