- Possible: Any adverse event occurring in a timely manner after the administration of the study treatment that follows a known pattern to the intervention and for which no other explanation is known. The adverse event, after careful consideration by the investigator, is considered to be unlikely related but cannot be ruled out with certainty.
- Probable: Any adverse event occurring in a timely manner after the administration of the study treatment that follows a known pattern to the intervention and for which no other explanation is known. The adverse event, after careful consideration by the investigator, is believed with a high degree of certainty to be related to the intervention
- Definitely Related: Any adverse event occurring within a timely manner after administration of the study treatment that is a known sequela of the intervention and follows a previously documented pattern but for which no other explanation is known. The adverse event is believed by the investigator to be incontrovertibly related to the intervention.

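### Most of the 1-year dose-limiting toxicity window is covered by a rule that collects only treatment-related events, under causality classes that overlap at the DLT boundary, so an event can be excluded without being recorded or centrally reviewed

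*Protocol article*

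**What the plan says.** **What is collected.** Appendix 4 (Adverse event definition and reporting) states: "All AEs are to be captured during treatment and only study-related AEs in the follow-up period". The main text (Follow-up evaluation) describes the same content for each visit: "CTCAE version 5.0 study treatment related toxicities recorded". Appendix 4 (Immediately reportable adverse events) asks for notification within 1 business day, but only of grade 3–5 reactions already classed as definitely, probably or possibly due to radiotherapy. The same section says that conditions unrelated to treatment are not SAEs in this protocol.

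**What counts.** Adverse events (main text) says that a grade 3–5 event listed in Table 3, without recurrence, "will automatically be considered to be possibly, probably or definitely related to treatment", unless there is clear evidence against it. A new drug with overlapping side effects, or a recurrence judged the more likely cause, also takes an event out. The DSMC makes the final decision where there is uncertainty.

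**How causality is graded.** Appendix 4 (Causality) first calls an event related if a causal link cannot be ruled out. It then defines five classes:
- 'Unrelated' opens with "Any adverse event for which there is evidence that an alternative etiology exists" and goes on to require that the event is clearly, beyond dispute, due to something else.
- 'Unlikely' covers events more likely due to the patient's condition or other therapy.
- 'Possible' is an event that "is considered to be unlikely related but cannot be ruled out with certainty".
- 'Possible', 'Probable' and 'Definitely Related' all also require the absence of any other known explanation.

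**The concern.** The DLT indicator is the only outcome in the dose-finding model. Under Dose assignment procedure, a patient with a grade 3–5 toxicity enters with weight 1. Any other patient enters as toxicity-free, with weight rising to 1 at 12 months. A DLT that is never recorded is therefore more than a missing value: it enters as evidence of safety at that level.

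Two features could cause this. First, the collection rule depends on relatedness, and no section says that events are recorded before they are attributed. A site that is confident an event is unrelated, drug-related or due to recurrence has no stated duty to record it, and the DSMC is called on only when there is uncertainty. Second, the wording that separates a DLT from a non-DLT contradicts itself, so two sites following the text could class the same event differently. At stake is whether the level declared to carry a risk of 35% or less really does.

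**Working it through.** **1. Design figures.** The protocol gives no figure for capture or attribution error. The design figures used below reproduce: 8 levels × 6 = 48 patients; 48/16 = 3 years (36 months) and 48/12 = 4 years (48 months), as stated.

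**2. Share of the window under the filter.** The window is 1 year, taken as 52 weeks. The protocol allows any fractionation, so the course length is an assumption of 1 to 6 weeks. Share after treatment = (52 − w)/52: for w = 1, 51/52 = 98%; for w = 6, 46/52 = 88%.

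**3. One event run through the rules.** Suppose a patient without recurrence but with known airway disease develops new grade 3 dyspnea at month 8 (hypothetical case).

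| Provision | Result |
|---|---|
| Automatic rule (dyspnea is in Table 3) | Related, a DLT, unless clear contrary evidence |
| General definition of related | Related, since causality cannot be excluded |
| 'Possible', closing sentence | Fits: thought unlikely but not excluded |
| 'Possible', 'Probable', 'Definitely Related', condition on other explanations | Fails all three: another explanation is known |
| 'Unlikely' | Fits, if the airway disease is judged the more likely cause |
| 'Unrelated' | Does not fit: not beyond dispute due to another cause |

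The event is a DLT under the first two provisions and a non-DLT if the class definitions are followed. If the site selects 'Unlikely' and treats the event as not related, the follow-up rule does not call for it to be collected, it is not immediately reportable, and the SAE carve-out can remove it from that route as well. Data collection asks for all SAEs within 24 hours, but with the carve-out this is not an unfiltered back-up.

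**4. Effect of lost DLTs on the 35% ceiling.** Let m be the share of true DLTs not recorded. The documents give no value, so m is assumed. Observed rate = true rate × (1 − m), so the true rate at an observed 35% is 0.35/(1 − m).

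| m | True 35% is seen as | Observed 35% is truly |
|---|---|---|
| 0 | 35.0% | 35.0% |
| 10% | 0.35 × 0.9 = 31.5% | 0.35/0.9 = 38.9% |
| 20% | 0.35 × 0.8 = 28.0% | 0.35/0.8 = 43.8% |
| 30% | 0.35 × 0.7 = 24.5% | 0.35/0.7 = 50.0% |

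**5. Illustrative simulation.** Taken from the protocol: the Table 4 risk estimates, start at Level 1, one-level escalation, 24 months of cumulative observation before escalating, and 48 patients. Assumed: a power model with normal prior variance 1.34, 14 patients per year, DLT times uniform over 12 months, 1,500 runs per setting, and two true-risk curves for Levels −1 to 6:
- A: 0.08, 0.11, 0.15, 0.20, 0.27, 0.35, 0.44, 0.54 (35% at Level 4)
- B: 0.15, 0.20, 0.27, 0.35, 0.44, 0.52, 0.60, 0.68 (35% at Level 2)

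Probability that the declared MTD has a true risk above 35%:

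| m | A | B |
|---|---|---|
| 0 | 0.21 | 0.26 |
| 10% | 0.33 | 0.47 |
| 20% | 0.53 | 0.65 |
| 30% | 0.68 | 0.82 |

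The values depend on the assumed curves, prior and m. The direction follows from how the model treats an unrecorded event.

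**The case against.** The strongest reply is that the provisions should be read together. The collection rule says study-related, not related in the site's prior opinion, and the automatic rule defines what is related. On that reading, a listed grade 3–5 event without recurrence is study-related by definition, is collected, and must be notified within 1 business day. Registration adds a reminder to all sites, at each new enrolment, to report new toxicities within 24 hours, with no attribution condition. Appendix 1 schedules adverse event assessments at 3, 6, 9 and 12 months. Much of this stands: a site reading the rules in that order keeps the listed events without recurrence. But no section fixes that order, the reminder does not say that events judged unrelated are included, and exclusions the site makes itself still go unreviewed unless it declares uncertainty. Appendix 4 also says "There is no time-limit for collection of AEs and SAEs after treatment within the 5-year follow-up period", but that sets how long events are collected, not which ones.

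A reader might infer more than the text supports, in four ways:
- *Any alternative cause makes an event 'Unrelated'.* It does not, because that class also requires the other cause to be beyond dispute. The overlap lies between 'Possible' and 'Unlikely'.
- *DLTs will be lost, or a particular share will be.* The documents show only that they can be.
- *Most dyspnea, pneumonitis or hemorrhage here has another explanation.* The documents give no data on this, and they exclude interstitial lung disease, prior symptomatic pneumonitis and persistent toxicity.
- *Leaving out recurrence-related events is itself an error.* It is part of the endpoint definition, and applied correctly it loses no DLT. What is missing is a record and a check of that decision.

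It is also fair to say that the automatic presumption can count events with other causes, which pushes the count up. The upward bias in the MTD is therefore relative to the endpoint as the protocol defines it.

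**Conclusion.** The point holds in this form. Over most of the DLT window (88–98% for an assumed course of 1 to 6 weeks), collection depends on relatedness. The order of collection and automatic attribution is not fixed, and a site's confident exclusion has no stated route to the DSMC. Separately, the causality classes contradict each other, the general definition and the automatic rule at the line that decides whether an event is a DLT. Because this is a conflict in current text, it is not a detail that an analysis plan could settle. An event that was never recorded may not be recoverable at analysis.

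Any resulting loss of DLTs moves the declared MTD upward. Its size cannot be derived from the documents. The figures of 38.9%, 43.8% and 50.0% for losses of 10%, 20% and 30%, and the simulated probabilities, are illustrations under assumed loss rates and not estimates for this trial.

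**What to change.** 1. **Record first.** Collect every grade 3–5 event of the Table 3 types to 12 months after treatment regardless of attribution, and say that the automatic rule is applied after recording. Align Follow-up evaluation and Immediately reportable adverse events with this. Point the Appendix 4 wording "any Grade 3-5 toxicity listed below will automatically be considered to be possibly, probably or definitely related to treatment" to Table 3, since Appendix 4 contains no such list.
2. **Review exclusions.** List each event that a site excludes (contrary evidence, new drug, recurrence), with its reason, for DSMC confirmation.
3. **Define the interim status.** The DSMC reviews events semi-annually, whereas dose levels are assigned patient by patient. State that a listed event without recurrence counts as a DLT in the model until its exclusion is confirmed, as the existing presumption implies.
4. **Reword the classes together.** Make 'Possible' a reasonable possibility that cannot be excluded even if other explanations exist, dropping both the statement that a link is unlikely and the bar on other explanations. Remove or soften that bar in 'Probable'. Narrow 'Unlikely' so that it no longer overlaps 'Possible'. Rewording 'Possible' alone would leave the overlap in place.

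Cost: amendment wording, a few more adverse event forms, and a short line listing for the existing DSMC.

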#### Radiation therapy adverse events

The rationale for this study is to determine the MTD for thoracic reirradiation implemented by increasing the amount of forgiveness applied to previously delivered dose. There is concern about RT effects on organs at risk, most notably central airway, bronchioles/alveoli, esophagus, pulmonary vessels, and heart/pericardium. It is currently unknown how different combinations of conventional and/or SBRT doses may interact to produce toxicity.

If there are baseline symptoms, such as grade 2 dyspnea, a toxicity will only be counted if the grade increases during follow up (for example: if the patient then develops grade 3 dyspnea, then it is counted as a grade 3 event, but if its stays as a grade 2 then it is not counted as a toxicity).

#### Causality (attribution)

In the absence of recurrence, any Grade 3-5 toxicity listed below will automatically be considered to be possibly, probably or definitely related to treatment (i.e. meeting the primary endpoint), unless there is clear evidence that the adverse event is either unrelated or unlikely to be related. The latter instance may occur, for example, in the case of a cardiac event in a patient with an upper lobe tumor and negligible heart dose, or esophageal issues in a patient who received negligible esophageal dose. If a patient starts a drug therapy with overlapping side effects, toxicity may be attributed to the new drug. If there is uncertainty, a final decision will be made by the members of the Date Safety Monitoring Committee (DSMC). See below for causality definitions.

In the setting of a recurrence, if a patient develops symptoms of an adverse event but deemed on balance more likely caused by a tumor recurrence than treatment (e.g. pulmonary hemorrhage in the presence of recurrence), this will NOT be considered a treatment-related toxicity.

An adverse event or reaction is considered related to the research intervention (i.e. radiotherapy) if there is a reasonable possibility that the reaction or event may have been caused by the research intervention (i.e. a causal relationship between the reaction and the research intervention cannot be ruled out by the investigator(s)). The relationship of an AE to the study treatment (causality) will be described using the following definitions:

- Unrelated: Any adverse event for which there is evidence that an alternative etiology exists or for which no timely relationship exists to the administration of the study treatment and the adverse event does not follow any previously documented pattern. The adverse event, after careful consideration by the investigator, is clearly and incontrovertibly due to causes other than the intervention.
- Unlikely: Any adverse event for which the time relationship between the study treatment and the event suggests that a causal relationship is unlikely and/or the event is more likely due to the subject’s clinical condition, or other therapies concomitantly administered to the subject.
- Possible: Any adverse event occurring in a timely manner after the administration of the study treatment that follows a known pattern to the intervention and for which no other explanation is known. The adverse event, after careful consideration by the investigator, is considered to be unlikely related but cannot be ruled out with certainty.
- Probable: Any adverse event occurring in a timely manner after the administration of the study treatment that follows a known pattern to the intervention and for which no other explanation is known. The adverse event, after careful consideration by the investigator, is believed with a high degree of certainty to be related to the intervention
- Definitely Related: Any adverse event occurring within a timely manner after administration of the study treatment that is a known sequela of the intervention and follows a previously documented pattern but for which no other explanation is known. The adverse event is believed by the investigator to be incontrovertibly related to the intervention.

